#### Follow-up

Patients will be followed up during hospitalization(t0), 3 months(t1), 6 months(t2) and 12 months(t3) after discharge through outpatient-clinic, hospitalization, telephone and other communication way. Content of follow-up is presented in Table 1.

**Table 1 Tab1:** Content of follow-up at different time points post-PCI

Assessments	t0	t1	t2	t3
**Daily living conditions**				
Low-salt and low-fat diet				
Proper exercise				
Quit smoking				
Quit drinking				
**Medications**				
**Use of medications for secondary prevention of CHD**				
Antiplatelet agents				
Statins				
ACEI/ARB				
β blocker				
** Medications meet the recommended dose**				
ACEI/ARB				
β blocker				
**Control of risk factors**				
**Blood pressure(≤ 130/80 mmHg)**				
** Blood glucose**				
Fasting blood glucose ≤ 6.0 mmol/L				
2 h postprandial blood glucose ≤ 11.0 mmol/L				
Glycosylated hemoglobin ≤ 6.5%				
** LDL-C(≤ 1.4 mmol/L)**				
**Outcomes**				
In-stent restenosis				
Severe ventricular arrhythmia				
Heart failure				
Recurrent angina pectoris				
Sudden cardiac death				
No reflow				
Atrial fibrillation				
Death from other causes other than cardiac death				
Stroke/cerebrovascular accident				

Including daily living conditions (whether to follow a low-salt and low-fat diet, whether there is proper exercise, whether to quit smoking, drinking, etc.), and whether to use medications for secondary prevention for CHD, including antiplatelet agents, statins, angiotensin-converting enzyme inhibitor(ACEI)/angiotensin II receptor(ARB), β blocker, and whether the dose of ACEI/ARB and β blocker meets the recommended dose, blood pressure control(≤ 130/80 mmHg), blood glucose control(fasting blood glucose ≤ 6.0 mmol/L, 2 h postprandial blood glucose ≤ 11.0 mmol/L, or glycosylated hemoglobin ≤ 6.5%), control of low-density lipoprotein cholesterol(LDL-C) (≤ 1.4 mmol/L) and occurrence of MACE which including in-stent restenosis, severe ventricular arrhythmia, heart failure, recurrent angina pectoris, and sudden cardiac death. The content of follow-up also includes no reflow, atrial fibrillation, occurrence of death from other causes other than cardiac death, and stroke/cerebrovascular accident. The definition of all outcomes is presented in Table 2.

**Table 2 Tab2:** Definition of the outcomes

Events (during hospitalization or follow-up)	Definition
In-stent restenosis	In-stent restenosis is defined if it is observed during coronary angiography reexamination
Severe ventricular arrhythmia	Including ventricular tachycardia, ventricular fibrillation captured by ECG or ECG monitoring
Heart failure	The patients had typical symptoms of heart failure (such as chest tightness, dyspnea, etc.) combined with cardiac ultrasound suggesting decreased cardiac systolic or diastolic function or accompanied by elevated NT-proBNP
Recurrent angina pectoris	If symptoms that are similar or even aggravated to previous angina symptoms like location, time, and degree of pain still occur after PCI
Sudden cardiac death	Sudden cardiac death due to coronary heart disease
No reflow	No coronary reflow or slow flow is observed during PCI or coronary angiography reexamination
Atrial fibrillation	Paroxysmal or persistent atrial fibrillation captured by ECG or ECG monitoring
Death from other causes other than cardiac death	Death from other causes other than cardiac death, such as stroke, cancer, etc
Stroke/cerebrovascular accident	Including ischemic stroke, hemorrhagic stroke diagnosed in hospital or through cerebral magnetic resonance imaging or diffusion weighted imaging report

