### Consent

Patients who do not meet the exclusion criteria and who meet all inclusion criteria may participate in this study. Researchers of the study including [name] and [name] will screen eligible patients for ACS diagnosis in the Chest Pain Center of multicenter and communicate with them or their agents about the general content of the study. These patients have every right to choose to participate in the study or not. These patients or their agents will be fully informed that participation in the study will not affect normal diagnosis and treatment, will not increase the risk of participants, and that participation or non-participation in the study will not affect patients' normal medical interests. However, participation in this study may provide new hope for improving the prognosis of patients with ACS. In addition, when patients or their agents agree to participate in the study, they could to choose how the clinical outcomes will be observed in different time point: by telephone, inpatient and outpatient medical records, or by contacting our researchers themselves and indicating on their informed consent. The dissemination of the results will occur through the publication of articles in international peer-reviewed journals, once the results are published, patients and their representatives will be notified by text or phone within a year. Those who agree to participate will sign informed consent.

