### Primary outcomes

Primary outcomes of this cohort are major adverse cardiovascular events within 1 year, including in-stent restenosis, severe ventricular arrhythmia, heart failure, recurrent angina pectoris, and sudden cardiac death.

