#### Blood sample and data collection

Peripheral blood samples of these patients were obtained within 24 h of admission and collected in heparin anticoagulant tube (2–4 mL). Samples were placed at room temperature for testing within 24 h. Clinical data of patients such as age, gender, history of hypertension, coronary heart disease and diabetes mellitus, body mass index (BMI), white blood cell count, level of hemoglobin, platelet, creatinine, aspartate aminotransferase (AST), alanine aminotransferase (ALT), lipid profile, left ventricular ejection fraction, left ventricular end-diastolic volume etc. were collected. The results of coronary angiography were recorded as well.

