### Additional supplementary instructions

This study is a non-interventional study, it will not involve vulnerable groups or interfere with routine diagnosis and treatment of participants, it will not affect any medical rights or increase the risk of participants either.

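### In-stent restenosis enters the primary MACE only if repeat angiography shows it, and re-imaging is left to routine care, so cases without other MACE are scored partly by who was re-imaged

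*Protocol article*

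**What the plan says.** The Primary outcomes section of the protocol article defines the primary outcome as "major adverse cardiovascular events within 1 year, including in-stent restenosis", followed by severe ventricular arrhythmia, heart failure, recurrent angina and sudden cardiac death. The Follow-up section refers the reader to Table 2 for the definitions of all outcomes. For restenosis, Table 2 says only: "In-stent restenosis is defined if it is observed during coronary angiography reexamination". It gives no degree of stenosis, no reason for the angiogram and no other route to the diagnosis.

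Four other places bear on how this component can be ascertained:

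- **Follow-up:** contact is made "through outpatient-clinic, hospitalization, telephone and other communication way". The visible rows of Table 1 cover lifestyle, medication, risk-factor control and outcomes. None is an angiogram.
- **Consent:** patients may choose to have outcomes observed "by telephone, inpatient and outpatient medical records, or by contacting our researchers themselves".
- **Blood sample and data collection:** the one sentence on collecting angiographic data, "The results of coronary angiography were recorded as well", stands with the admission sample and clinical data.
- **Additional supplementary instructions:** the study is non-interventional, and "it will not involve vulnerable groups or interfere with routine diagnosis and treatment of participants".

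Recurrent angina, by contrast, is defined in Table 2 by symptoms alone: "If symptoms that are similar or even aggravated to previous angina symptoms like location, time, and degree of pain still occur after PCI".

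**The concern.** Detection of restenosis depends on a test that the study, as far as the text shows, neither orders nor tracks. Take two patients with the same in-stent lesion, no angina and no other MACE component. If one is re-imaged as local routine and the lesion is seen, that patient has a primary event. The other, never re-imaged, is event-free. Better telephone contact or record retrieval cannot close this gap, because there is no angiogram to retrieve.

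The Statistical analysis section compares indicators, takes the significant ones into stepwise logistic regression, and runs ROC analysis with a cut-off. It does not separate patients who were re-imaged and clear from patients who were never re-imaged. If the chance of repeat angiography differs between the three hospitals, between ACS types, or with another factor related to the markers, part of any marker-MACE association would reflect who was re-imaged. Sensitivity, specificity and the cut-off would be affected too.

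**Working it through.** **Textual check.** Reading the sections together:

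1. Restenosis is in the primary composite (Primary outcomes).
2. It counts only when seen at repeat angiography (Table 2).
3. No visible row or sentence schedules repeat angiography, and routine care is not altered (Table 1, Follow-up, Additional supplementary instructions).
4. A counted case therefore needs both restenosis and re-imaging in routine care.
5. Recurrent angina needs no angiogram (Table 2), so a patient with restenosis and recurrent angina is MACE-positive either way. The exposed group is restenosis without angina or any other MACE component.

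**Illustration of size.** The documents give neither a restenosis rate nor a re-angiography rate, so there is no figure to reproduce and both are assumed.

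- *r*: true restenosis rate, the same in both marker groups, so there is no true association (assumed 10%; range 5% to 15%).
- *a*: proportion re-imaged (assumed 40% versus 20%).
- *m*: other MACE in each group (assumed 8.1%). This borrows the planning rate in the Sample size section, 151 of 1864. The MACE definition behind that rate is not shown.
- *f*: share of detected cases that add a new MACE patient (1 = no overlap with other components; 0.5 = half already count).

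Formulas:

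- Detected restenosis = *r* × *a*.
- Component RR = (*r* × *a*₁)/(*r* × *a*₂) = *a*₁/*a*₂.
- Composite rate = *m* + *f* × *r* × *a*.

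| *r* | Re-imaged | Detected | Component RR | Composite, *f* = 1 | Composite, *f* = 0.5 |
|---|---|---|---|---|---|
| 10% | 40% vs 20% | 4% vs 2% | 2.0 | 12.1/10.1 = 1.20 | 10.1/9.1 = 1.11 |
| 5% | 40% vs 20% | 2% vs 1% | 2.0 | 10.1/9.1 = 1.11 | 9.1/8.6 = 1.06 |
| 15% | 40% vs 20% | 6% vs 3% | 2.0 | 14.1/11.1 = 1.27 | 11.1/9.6 = 1.16 |
| 10% | 50% vs 10% | 5% vs 1% | 5.0 | 13.1/9.1 = 1.44 | 10.6/8.6 = 1.23 |
| 10% | 20% vs 20% | 2% vs 2% | 1.0 | 10.1/10.1 = 1.00 | 9.1/9.1 = 1.00 |

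In the last row there is no spurious association, but 80% of true restenoses go uncounted as restenosis.

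**Event numbers.** At the planning rate, 150 × 0.081 = 12.15 patients with MACE, or 135 × 0.081 = 10.9 after 10% loss. With so few events, a handful of selectively detected cases can change which markers are selected.

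**The case against.** The case on the other side has real force, and several stronger readings that a reader might infer are not supported.

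- **That the component shows who was re-catheterised instead of who restenosed.** It does not. A counted case still needs restenosis to be seen.
- **That restenosis is the only component that depends on tests.** Table 2 also requires arrhythmia to be captured on ECG or monitoring, and heart failure to be backed by ultrasound or NT-proBNP. Ascertainment through routine care is normal in an observational cohort. What is particular to restenosis is that its definition rests solely on repeat invasive imaging.
- **That every un-imaged patient with restenosis is scored event-free.** Those with recurrent angina or another component already count.
- **That MACE risk could appear doubled.** The 2.0 belongs to the component. Under the same assumptions the composite shows about 1.1 to 1.2, and nothing in the documents shows that re-imaging differs by marker level.
- **That the undetected restenoses rival the expected number of MACE.** That would set assumed true lesions, silent ones included, against a planning rate whose MACE definition is not shown. The two are not comparable.
- **That no visit includes angiography.** Fig. 1 and the cell marks of Table 1 are not shown, so a scheduled angiogram cannot be wholly excluded, although no row or sentence mentions one and the non-interventional statement points against it. Inpatient and outpatient records, where a repeat angiogram would appear, are also permitted sources.

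It can also be said that an article may leave a threshold or form fields to the full protocol. That carries some weight for the form fields. It carries less for the definition, since the article presents Table 2 as the definition of all outcomes. Finally, a symptom-driven definition overlaps with recurrent angina and still depends on who is referred. That is true. But because such patients mostly count through angina anyway, the composite would then depend far less on re-imaging.

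**Conclusion.** The point holds in a limited form. As written, the restenosis component requires both a lesion and a repeat angiogram done in routine care. Patients without angina or another MACE component are therefore scored according to whether they happened to be re-imaged. This biases the marker-MACE association only if re-imaging is related to the markers, directly or through hospital, ACS type or another factor. Otherwise the result is under-counting.

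On the main assumed case, the spurious composite relative risk is about 1.2 with no overlap and about 1.1 with half overlap. Over the range tried it runs from 1.0 (equal re-imaging) to 1.44 (50% versus 10% re-imaged, no overlap). All of this rests on assumed restenosis, re-imaging and overlap rates, and on 8.1% as a stand-in for other MACE. The sponsor should correct it because the remedy is cheap; it does not invalidate the study.

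**What to change.** 1. In Primary outcomes and Table 2, restrict the MACE component to restenosis found at angiography done for recurrent symptoms or objective ischaemia, with a stenosis threshold that the sponsor states.
2. At each follow-up, record whether, when and why angiography was repeated.
3. Report incidental restenosis outside MACE, with the number of patients re-imaged as denominator.
4. Do not label patients without repeat angiography as free of restenosis. Describe them as having no clinically driven restenosis.
5. Add a sensitivity analysis of MACE without the restenosis component.

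The cost is slightly fewer events in a composite that already expects few, about two extra form fields, and a formal amendment. The section on modification of the protocol requires research group agreement, ethics approval, and reporting to participants and the registry for a change to outcome indicators. No procedure is added and patient care does not change.

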### Study design and setting

This is a multicenter, prospective, observational, longitudinal cohort study that will be carried out between December 2022 to December 2024. Three centers participate in this study, including The Affiliated Hospital of Guizhou Medical University which is also the host of this study,  the First People’s Hospital of Guiyang and the Second People’s Hospital of Guiyang. The study will be conducted in accordance with the Declaration of Helsinki (as revised in 2013). Ethics approval for the trial was obtained only from the main center—Ethics Committee of The Affiliated Hospital of Guizhou Medical University (Medical Research Ethics Review 2022. No. 2022117 K). Written informed consent will be obtained from the patients. This study was registered at Chinese Clinical Trial Registry (ChiCTR) (No. ChiCTR2200066382). The outcomes will be assessed during hospitalization and at four follow-up times (during hospitalization, 3, 6, 12 months after discharge).

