### Inclusion criteria

i) Patients initially diagnosed as ACS according to the 2020 European Society of Cardiology(ESC) guideline [14] and went through PCI. The diagnosis of acute myocardial infarction includes symptoms (like chest discomfort), electrocardiogram (ECG) showing that characteristic abnormalities include ST-segment and T-wave changes, and elevation of a cardiomyocyte biomarker especially high-sensitivity cardiac troponin T (hs-cTnT). The diagnosis criteria of UA is that history (such as risk factors for CHD), symptoms (initial or aggravation angina pectoris in 1 month), and ECG showing that ST-segment depresses or T wave changes without the elevation of cardiomyocyte biomarker; ii) Duration of onset of patients ≤ 2 weeks; iii) The range of age is 18–100 years old; iv) Patients who are willing to comply with the protocol, can understand the purpose of the study, voluntarily participate in the study or legal guardian signed the informed consent.

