### Secondary outcomes

Secondary outcomes include the occurrence of these condition within 1 year: i)No reflow after PCI (after reperfusion treatment, blood flow of coronary artery is slowed down or completely absent); ii)Atrial fibrillation; iii) All-cause death except cardiovascular death; iv) Stroke/cerebrovascular accident.

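### Heart failure and ventricular arrhythmia count as MACE from the index admission with no new-onset or after-sampling condition, so events already present at the blood draw can be scored as predicted outcomes

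*Protocol article*

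**What the plan says.** **When counting starts.** The Follow-up section states: "Patients will be followed up during hospitalization(t0), 3 months(t1), 6 months(t2) and 12 months(t3) after discharge". Study design and setting adds: "The outcomes will be assessed during hospitalization and at four follow-up times". The event column of Table 2 is headed "Events (during hospitalization or follow-up". The Primary outcomes section gives the window as "Primary outcomes of this cohort are major adverse cardiovascular events within 1 year" and names no starting point.

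**How events are defined (Table 2).** Heart failure is typical symptoms, with chest tightness and dyspnea as examples, "combined with cardiac ultrasound suggesting decreased cardiac systolic or diastolic function or accompanied by elevated NT-proBNP". Severe ventricular arrhythmia is VT or VF captured by ECG or ECG monitoring. Atrial fibrillation, a secondary outcome, is any paroxysmal or persistent episode captured the same way. The Secondary outcomes section describes no-reflow as "No reflow after PCI (after reperfusion treatment, blood flow of coronary artery is slowed down or completely absent", and Table 2 allows it to be observed during PCI.

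**When the markers are measured.** "Peripheral blood samples of these patients were obtained within 24 h of admission". The draw is not tied to PCI or to any event.

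**Who enters.** Inclusion criterion ii, "Duration of onset of patients", allows up to two weeks. The exclusion criteria name certain cardiomyopathies, severe valvular disease and a history of severe cardiogenic shock. They do not name heart failure or VT/VF at presentation.

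**How it is analysed.** Statistical analysis plans stepwise logistic regression to find predictors, followed by ROC analysis.

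**The concern.** The stated aim is to relate marker levels to MACE over the following year. That requires the marker to be measured before the event. Under the written rules, a patient admitted in heart failure and sampled some hours later is an enrolled participant, has a marker value, and is also a primary-outcome event. The same holds for a patient whose VT or VF was recorded on arrival.

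The Discussion itself says that myocardial necrosis triggers the immune response, and it links CD8-positive T-cell numbers to infarct area and ventricular dysfunction. On that reasoning, the acute event could raise a marker and also produce early heart failure. An association could then appear, and an ROC cut-off be chosen, even for a marker that says nothing about later events. With few events expected, a handful of such cases could drive the result.

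**Working it through.** **1. The plan's own figures.** The Sample size section gives 1-year MACE in ACS as 151/1864 = 8.1%, against 0.05% in healthy people, and a size of 125. The usual two-proportion formula is

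n = [z(0.975)·√(2·p̄·(1−p̄)) + z(0.90)·√(p1(1−p1) + p2(1−p2))]² / (p1−p2)²

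With p1 = 0.081, p2 = 0.0005 and p̄ = 0.04075:

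- numerator: (1.960×0.2796 + 1.2816×0.2737)² = 0.8079
- denominator: 0.0805² = 0.00648
- n = 124.7, so 125 per group

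The 90% power and two-sided test are assumptions, because the article states neither. Only the 8.1% is needed below; this point does not dispute the 125.

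**2. Which MACE components can be met at or before the draw.**

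| Component | Condition in Table 2 | Can the presenting ACS itself meet it? |
|---|---|---|
| In-stent restenosis | seen at repeat angiography | No |
| Severe ventricular arrhythmia | any VT/VF recorded | Yes |
| Heart failure | symptoms plus ultrasound or NT-proBNP finding; no threshold, no change from admission | Yes |
| Recurrent angina | must occur after PCI | No, although it could precede a late draw |
| Sudden cardiac death | death | No |

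So two of the five are open. Among the secondary outcomes, no-reflow at the index PCI precedes any sample drawn after PCI, and atrial fibrillation has no time condition at all.

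**3. Whether the analysis can restore the order.** The logistic outcome is event yes or no. Recording at t0, t1, t2 and t3 separates the index stay from the later periods. It does not place an event before or after the draw within the index stay.

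**4. Illustration of size.** Let q be the share of patients who already meet heart failure or VT/VF at or before the draw. The document gives no value, so q is assumed. Without contamination, the expected events are 150 × 0.081 = 12.15, or 135 × 0.081 = 10.9 after the stated 10% loss. With contamination:

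- prevalent events = 150·q
- later events among the rest = 150·(1−q)·0.081
- prevalent share w = q / [q + (1−q)·0.081]

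| q (assumed) | Prevalent | Later | Prevalent share |
|---|---|---|---|
| 5% | 7.5 | 11.5 | 39% |
| 10% | 15.0 | 10.9 | 58% |
| 20% | 30.0 | 9.7 | 76% |
| 30% | 45.0 | 8.5 | 84% |

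**5. Effect on the ROC.** Suppose a marker is unrelated to later events but lies 0.5 SD higher in prevalent cases (also assumed). Its area under the curve for counted MACE is about w·Φ(0.5/√2) + (1−w)·0.5, where Φ(0.354) = 0.638. For q = 5%, 10%, 20% and 30% this gives 0.55, 0.58, 0.60 and 0.62, where the value for later events is 0.50. Over shifts of 0.3 to 0.8 SD the range is 0.53 to 0.68.

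**The case against.** Much can fairly be said on the other side.

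- **Scope.** Three of the five components cannot be met by the presenting ACS, and no-reflow is not part of MACE. A reader might infer that the primary outcome as a whole is open to this problem; Table 2 does not support that. This stands.
- **Heart failure wording.** Table 2 asks for typical heart-failure symptoms plus an objective finding. A reader might infer that the chest discomfort used for the ACS diagnosis is enough; the text does not say so. This stands, but genuine heart failure at presentation would still count.
- **Size.** No passage supports any value of q. The 8.1% comes from another cohort whose MACE definition and counting window are not shown; if it already includes in-hospital events, adding prevalent ones partly double-counts. This stands, so the tables above show sensitivity and are not estimates.
- **Mechanism.** A reader might infer that the associations will be reverse causation produced by infarct size. The text shows only that prevalent events can enter. Moreover, 50 of the 150 patients have unstable angina, which is defined without biomarker elevation.
- **Recoverability.** The aim is prospective in intent, and t0 to t3 are recorded separately, so post-discharge events can be isolated. It would be too strong to say that the study cannot answer its question. However, the article does not plan that separation, and it would not order events within the index stay.
- **Condensed article.** Covariates and sensitivity analyses are commonly left to a fuller document, and the spread in time from onset to sample is a separate matter. But Table 2 is presented as the definition of all outcomes, and the sampling window is explicit. These are stated rules, not omitted detail.

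**Conclusion.** The point holds for heart failure and severe ventricular arrhythmia, two of the five MACE components, and in the same way for the secondary outcomes no-reflow and atrial fibrillation when the sample follows the event. Applied as written, the plan can count events already present at or before the blood draw as outcomes predicted by the markers, and the logistic model cannot tell them apart.

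The amount of contamination cannot be derived from the document. What can be said is that about 12 events are expected in 150 patients if the 8.1% applies, so few misplaced events are needed to matter: at an assumed 5% of patients, about 8 prevalent events would be about 39% of those counted. This is a defect in the outcome definition that should be corrected. It does not show that any association found would be spurious, or that the data could not be rescued.

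**What to change.** 1. In Table 2, count heart failure and severe ventricular arrhythmia as MACE only if they are new, or worsened from admission status, with onset after the blood draw.
2. Record heart failure or VT/VF present at or before the draw as a baseline covariate.
3. Report MACE from discharge to 12 months as a sensitivity analysis, using the existing t0 to t3 recording. It is better kept out of the primary role, because starting at discharge discards genuine in-hospital events that follow the sample.
4. Relate no-reflow to the markers only in patients sampled before PCI, and apply the same after-the-draw condition to atrial fibrillation.

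**Cost.** These are changes to definitions and analysis wording; patient care and the sampling schedule stay as they are. There will be fewer counted events in a study that already expects few. Draw, PCI and event times must be taken from the medical record; the article does not say that they are collected, so the data form may need these fields.

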### Exclusion criteria

i) Patients with dilated cardiomyopathy, hypertrophic cardiomyopathy, history of severe cardiogenic shock, active endocarditis, rheumatic heart disease, or severe valvular disease, severe hepatic or renal dysfunction, severe hemorrhagic diseases, severe infectious diseases, severe respiratory diseases, hematological diseases, autoimmune diseases and craniocerebral diseases, malignant tumors, pulmonary embolism, ventricular septal perforation and aortic dissection; ii) Patients with a serious medical condition or a life expectancy of less than 12 months; iii) Patients with a history of allergy to contrast media; iv) Patients contraindicated with antithrombotic therapy; v) Patients lack of medication compliance and could not take secondary prevention drugs regularly for CHD as required; vi) Patients participated in another clinical trial that had not yet completed or had completed for less than 3 months.

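### The secondary atrial fibrillation outcome has no new-onset condition and known AF is not excluded, so AF that predates the ACS can be counted as a 1-year occurrence

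*Protocol article*

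**What the plan says.** The section on secondary outcomes lists AF as item ii under the lead-in "Secondary outcomes include the occurrence of these condition within 1 year". The Follow-up section refers to Table 2 for the definitions of all outcomes. There the AF row reads "Paroxysmal or persistent atrial fibrillation captured by ECG or ECG monitoring", in a column headed "Events (during hospitalization or follow-up)".

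The timing is given under Follow-up: "Patients will be followed up during hospitalization(t0), 3 months(t1), 6 months(t2) and 12 months(t3) after discharge". The first assessment is thus the index stay itself.

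The exclusion criteria name several cardiac conditions, beginning "Patients with dilated cardiomyopathy, hypertrophic cardiomyopathy, history of severe cardiogenic shock, active endocarditis, rheumatic heart disease, or severe valvular disease". The item nearest to AF is "Patients contraindicated with antithrombotic therapy", which does not remove patients with AF. None of items i to vi names AF or a previous arrhythmia, and the age range runs to 100 years.

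The baseline data are described as "Clinical data of patients such as age, gender, history of hypertension, coronary heart disease and diabetes mellitus", followed by further items and an open ending. AF history is not among the items named.

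**The concern.** A 1-year outcome should record something that arises during the year. The AF row instead records a state: AF is seen on a tracing, whenever it began. Someone who has lived with persistent AF for years and shows it on the admission tracing meets the rule at the first assessment and at any later one.

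Two results would suffer. The reported 1-year AF rate would blend prevalence with incidence. Any analysis of markers against AF would also be distorted, because the blood sample is taken within 24 hours of admission and, for pre-existing AF, the condition came before the marker. If patients with long-standing AF tend to be older or to have more chronic disease, a marker that merely tracks age or comorbidity would seem to predict AF. The Statistical analysis section plans stepwise logistic regression for predictors of the target outcomes. That is a yes/no analysis, in which event timing plays no part and cannot separate old AF from new.

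**Working it through.** **Step 1: the text applied to three patients.**

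| Patient | Meets the AF row? | Arose within the year? |
|---|---|---|
| A: persistent AF for years, seen on the admission ECG | Yes, at t0 | No |
| B: no earlier AF, first episode recorded at month 4 | Yes | Yes |
| C: no AF recorded | No | No |

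A and B receive the same value. Patient A's AF is likely to be seen, because an ECG is part of the diagnosis at entry. For infarction the inclusion criteria ask for "electrocardiogram (ECG) showing that characteristic abnormalities include ST-segment and T-wave changes", and for unstable angina they also ask for ECG changes.

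**Step 2: comparison with other rows of Table 2.** Recurrent angina must arise after PCI, and restenosis must be found at repeat angiography. Both are anchored in time by their own wording. The AF row has no such anchor.

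**Step 3: illustration of size.** The document gives no AF figure, so there is nothing to reproduce. Only N = 150 comes from the protocol (Sample size). The rest is assumed:

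- p, AF before the ACS: 2% to 15%
- c, share of those patients whose AF is recorded in hospital or later: 50% to 100%
- r, 1-year risk of new AF in the others: 3% to 10%

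Loss to follow-up is ignored.

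Pre-existing cases counted = 150 × p × c. 
New cases = 150 × (1 − p) × r. 
Share pre-existing = pc / [pc + (1 − p)r]. 
Apparent rate = pc + (1 − p)r, to be compared with r.

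| p | c | r | Pre-existing | New | Share | Apparent rate | Rate of new AF |
|---|---|---|---|---|---|---|---|
| 2% | 50% | 10% | 1.5 | 14.7 | 1.5/16.2 = 9% | 10.8% | 10% |
| 5% | 100% | 5% | 7.5 | 7.1 | 7.5/14.6 = 51% | 9.8% | 5% |
| 15% | 100% | 3% | 22.5 | 3.8 | 22.5/26.3 = 85% | 17.55% | 3% |

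The first and last rows are the extremes of the assumed ranges.

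**Step 4: direction.** Apparent rate minus r equals p(c − r). In the middle row this is 0.05 × (1 − 0.05) = 0.0475, which takes 5% to 9.75%. The rate is inflated whenever known AF is more likely to be recorded than new AF is to arise (c > r). That holds throughout the assumed ranges, where c is at least 50% and r at most 10%.

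**The case against.** The best reply is that Table 2 should be read together with the list of secondary outcomes. That list speaks of occurrence within a year, and the table heading speaks of events. Both words ordinarily mean something that arises in the window. On this reading the AF row only sets the standard of proof, namely an ECG or monitoring record. This shows that incident AF may well be intended. It does not settle the scoring, because the article names Table 2 as the definition of all outcomes and the AF row does not carry that meaning through.

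A second reply is that a journal article leaves baseline fields and at-risk sets to the full protocol or analysis plan. This stands in part. The baseline list is open-ended, so a reader who infers that AF history will not be collected goes beyond the text. The point rests on the scoring rule that is printed, not on the missing field.

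A third reply limits the reach. A reader might infer that every patient with earlier AF is an event on day one. The text does not support that: earlier paroxysmal AF in a patient now in sinus rhythm counts only if an episode is recorded later. The row also names only paroxysmal and persistent AF and is silent on permanent AF. The exclusion of cardiomyopathy, rheumatic and severe valvular disease may lower the prevalence of AF at entry.

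Finally, the study aim, the sample size and the ROC cut-off all concern MACE. No model specific to AF is set out, so the harm to an AF analysis depends on AF being treated as one of the target outcomes. This limits the weight of the point but does not remove it, since AF is a declared secondary outcome.

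**Conclusion.** The point holds for a secondary outcome. Followed as written, the rule counts AF from before the ACS as a 1-year occurrence whenever it is recorded in hospital or later. The AF rate is then a mixture of prevalent and incident cases, inflated under the mild condition in Step 4, and any association between markers and AF is biased.

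The size is unknown. The 9% to 85% range shows only how far the answer depends on assumed inputs, and no percentage should be cited as an estimate for this cohort. A narrower set (prevalence 3% to 10%, new AF 5% to 10%, every known case recorded) gives 24% to 69%, but those inputs are no better grounded in the document.

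A reader might also infer that the primary result is compromised. It is not: AF is not a component of MACE in either the abstract or the Methods, and the sample size does not use it. Nor does the problem imply that all AF on the admission ECG is old disease. The onset of ACS may be up to 2 weeks before enrolment, so AF first triggered by the index ACS can already be present at admission.

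**What to change.** Reword the AF row of Table 2 as new-onset AF: first documented AF during the index hospitalization or follow-up in patients with no AF history before the index ACS. With it:

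- Record AF history at baseline from the medical record.
- Take patients with prior AF out of the at-risk set for this outcome only, keep them in all other analyses, and report prior AF as a baseline characteristic.
- Report first-ever AF that is already present on the admission ECG, or that precedes the blood sample, as a separate category. Do not discard it. A sensitivity analysis can leave it out of models that claim prediction from the markers, since in those cases the marker did not come first.

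The cost is one table row and one record-based field. The article already describes a route for formal changes to outcome indicators (Modification of the protocol). The downside is a somewhat smaller denominator and fewer events. At the assumed 5% prevalence, 150 × 0.95 = 142.5 patients would remain at risk and about 7 events would be counted instead of about 15.
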